#### Data management

Data related to the trial will be anonymized and recorded in password-protected case report forms (CRFs). Only authorized researchers will have access to the CRFs. No interim analysis will be performed prior to the end of the study. The collected data will be kept for 5 years after the end of the study and will be destroyed after that.

#### Data analysis

All statistical analyses will be performed using SPSS® Statistics (version 24.0; IBM Corp., Armonk, NY, USA). The Shapiro–Wilk test will be used to evaluate the normality of the data. The primary outcome will be analyzed using the independent *t* test or Mann–Whitney test, depending on the normality of the data. The secondary outcomes will be analyzed using a linear mixed model or generalized estimating equation. *P* values < 0.05 will be considered statistically significant. Both intention to treat and per protocol analyses will be performed.

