### Outcome measures

The primary outcome of the study is the change in ROM (flexion or abduction) in the affected shoulder between baseline and 12 weeks. Flexion, abduction, external rotation, and internal rotation will be measured both passively and actively in a sitting position. External and internal rotation will be measured with the shoulder abducted to 90° or as much as possible. ROM will be measured using a goniometer. Measurements will be performed on enrollment, and 4, 8, and 12 weeks thereafter, by a physical or occupational therapist blinded to the group assignments.

The secondary outcomes of this study are pain, functional outcomes, and quality of life. The intensity of pain in the affected shoulder will be measured using a numerical rating scale (NRS), which is a simple and commonly used method for rating pain intensity from 0 (*no pain*) to 10 (*worst pain imaginable*) [14]. Both maximum pain and general pain will be measured at each visit: maximum pain refers to the most intense pain experienced during the week before the visit, and general pain represents the average pain intensity during that week. Functional outcomes will be measured using the short-form version of the Disabilities of the Arm, Shoulder and Hand questionnaire (QuickDASH), a widely used self-report measure of upper extremity disability [15]. Higher QuickDASH scores reflect poorer functional outcomes. Quality of life will be measured using the Functional Assessment of Cancer Therapy-Breast (FACT-B) and EuroQol Five-dimensional (EQ-5D-5L) instruments. The FACT-B scale consists of 37 items and is specifically aimed at breast cancer patients. The four subdomains of FACT-B are physical, social/family, emotional, and functional well-being. Higher FACT-B scores reflect better the quality of life [16–18]. The EQ-5D-5L questionnaire captures health status based on five dimensions: mobility, self-care, usual activities, pain/discomfort, and anxiety/depression [19]. Each dimension is scored from 1 to 5, and health status is summarized as a five-digit code: “11111” represents no problems in any of the five dimensions, and “55555” represents the worst possible health status. Higher EQ-5D-5L scores indicate better health status [20]. Secondary outcomes will also be assessed, on enrollment and 4, 8, and 12 weeks thereafter. Time schedule of enrollment, interventions, assessments are presented in Fig. 1.

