### Statistical analysis

#### Sample size

The standard deviation of ROM in the affected shoulder is expected to be 23°, and the difference in ROM between groups is expected to be 15° based on a previous study [9] and our own unpublished preliminary study. Using two-sample *Z* tests, and assuming homogeneity of variance, the sample size was estimated at 37 for each group with an alpha level of 5% and power of 80%. With an expected dropout rates of 20%, at least 47 participants are needed in each group, so enrollment of 100 participants (*n* = 50 per group) is planned.

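### A normality test on the trial's own data decides whether the primary analysis compares means or ranks, although the trial is sized on a mean difference

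*Protocol article*

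**What the plan says.** The protocol article defines the endpoint under Outcome measures: "The primary outcome of the study is the change in ROM (flexion or abduction) in the affected shoulder between baseline and 12 weeks".

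Under Data analysis it sets a two-step rule. First, "The Shapiro–Wilk test will be used to evaluate the normality of the data". Then, "The primary outcome will be analyzed using the independent *t* test or Mann–Whitney test, depending on the normality of the data". No single primary test is named.

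The Sample size section plans on one quantity only. It states that "The standard deviation of ROM in the affected shoulder is expected to be 23" degrees and that "the difference in ROM between groups is expected to be 15" degrees. It then uses a two-sample Z test: "assuming homogeneity of variance, the sample size was estimated at 37 for each group". That is a calculation for a difference in means.

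**The concern.** The two branches do not answer the same question. The t test compares mean change in degrees. Mann–Whitney asks whether values in one arm tend to rank above those in the other. The two agree on a common quantity only if one arm is a pure shift of the other, which nothing in the protocol guarantees.

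The trial was planned to detect a mean difference of 15°. If the normality test rejects, the primary P value no longer refers to that quantity, and a reader cannot tell before the data are in which comparison will carry the trial's conclusion.

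This is not a detail left to an unseen analysis plan. The article states the data-dependent rule outright, so the objection is to what it fixes.

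**Working it through.** **Inputs from the protocol article.** Difference 15°, SD 23°, alpha 5%, power 80%, dropout 20%, 50 per group planned (Sample size); 1:1 allocation (Randomization section); change in ROM to 12 weeks (Outcome measures); t test or Mann–Whitney chosen by Shapiro–Wilk (Data analysis).

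**Assumptions, not in the document.** Shapiro–Wilk level 0.05; applied to each arm separately or to both arms pooled; the distribution shapes listed below.

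**Step 1: reproduce the plan's figures.** Per group, n = 2(z₀.₉₇₅ + z₀.₈₀)² × SD² / difference² = 2 × (1.960 + 0.842)² × 23² / 15² ≈ 36.9, so 37. With dropout, 37 / (1 − 0.20) = 46.25, so 47. Both match. A t test instead of a Z test needs 38. With 50 × 0.80 = 40 evaluable per arm, power is 83.1% (Z) or 82.1% (t). A fixed mean-based test therefore needs no larger sample.

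**Step 2: switch rate with exactly normal data.** If either arm's rejection triggers the switch, the rate is 1 − 0.95² = 9.75%. Simulation gives 10.0% per arm and about 5% pooled.

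**Step 3: simulate the whole rule.** 40 per arm, SD 23°, same shape in both arms, 4,000 runs per setting. Switch rates are per arm / pooled. Power is at a 15° shift with per-arm testing.

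| Assumed shape | Switch, no difference | Switch, 15° shift | Power: t test | Power: Mann–Whitney | Power: two-step rule | t and Mann–Whitney disagree at 15° |
|---|---|---|---|---|---|---|
| Normal | 10.0% / 4.9% | 10.0% / 4.6% | 82.4% | 80.1% | 82.2% | 4.7% |
| t, 5 df | 51.6% / 49.7% | 52.2% / 41.8% | 82.0% | 88.0% | 87.1% | 8.7% |
| Gamma, shape 4 | 83.1% / 89.3% | 83.1% / 74.0% | 81.4% | 86.4% | 86.3% | 7.3% |
| Lognormal, sigma 0.5 | 97.9% / 99.3% | 97.9% / 93.9% | 82.1% | 93.3% | 93.4% | 11.5% |

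With no difference between arms, the two-step rule rejected in 4.4% to 5.4% of runs across all settings.

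**Step 4: how often the switch changes the conclusion.** With normal data, a run of the same design found that the two-step verdict differed from the t-test verdict in 0.7% of trials at a 15° shift and in 0.4% with no difference. For the non-normal shapes at 15° it differed in 6% to 12%, where the switch mostly raised power.

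**Step 5: equal means, different shapes.** With one normal arm and one left-skewed arm (mirrored lognormal) of equal mean, the rule switched in 85.4% of trials. It rejected in about 7.2%, against 5.1% for the t test. Mann–Whitney was responding to a difference in shape, not in means.

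**The case against.** The strongest defence is that the rule is fully pre-stated: version 1.0 was finalized in March 2020, before recruitment began in April 2020, and it gives the analyst no free choice between tests. It also performs well. Type I error holds when the arms share a shape, and at a 15° shift the rule gains about 5 points of power over the t test for the t or gamma shape and about 11 for the lognormal. With normal data the switch hardly ever changes the verdict. All of this stands. It limits the point to what is estimated.

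Several stronger readings are tempting and are not supported:

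- A reader might infer inflated type I error. That appears only in the assumed case of equal means with different shapes.
- A reader might infer that the pre-test gains nothing. The power columns show otherwise for non-normal shapes.
- A reader might infer that the Mann–Whitney branch cannot give a result in degrees. A Hodges–Lehmann shift with a confidence interval would be in degrees, although it equals the mean difference only under a pure shift. The article specifies no estimate for either branch and may leave that to the full plan.
- A reader might argue that a ROM ceiling and rounded goniometer readings make a switch likely. The protocol states neither a measurement cap nor a rounding rule; its 180° values are exercise targets.
- A reader might fault Mann–Whitney for not adjusting for baseline or hospital. The same is true of the independent t test named beside it.

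Which data are given to the Shapiro–Wilk test is a detail an article may omit. It is treated here as an assumption, not as a fault.

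**Conclusion.** The concern holds as a defect in what the primary analysis estimates. The quantity tested is settled by the data, while the sample size rests on a mean difference alone.

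In size, about 10% of trials with exactly normal data would switch if each arm is tested at 0.05, and about 5% if pooled. For the non-normal shapes tried, the rate runs from about 42% to 99%. These show how strongly it depends on shape and are not a forecast for this trial. The rates rest on 40 evaluable per arm, SD 23° and an assumed 0.05 level.

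A reader might conclude that the sample size is wrong or the trial's error rate compromised. Neither follows: 37 and 47 per group reproduce, and rejection under a common shape stays near 5%. The point is worth correcting because the correction is cheap, not because the trial would otherwise be invalid.

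**What to change.** Delete the normality gate for the primary outcome and name one primary analysis: an ANCOVA of week-12 ROM on group and baseline ROM. Report the adjusted mean difference in degrees with its 95% CI, whatever the Shapiro–Wilk result. Keep Mann–Whitney as a named sensitivity analysis.

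This respects the endpoint as defined. With baseline ROM in the model, analysing change or the week-12 value gives the same group difference, because change is the week-12 value minus a covariate already fitted.

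The cost is a sentence or two of wording. Baseline and week-12 ROM are already collected, no more patients are needed, and the change can be made at any time before unblinded analysis. The downside is some loss of power relative to a rank test if the data prove heavy-tailed or skewed: roughly 5 points in the assumed t and gamma settings and about 11 in the lognormal, all without baseline adjustment. Adjustment offsets this to the extent that baseline ROM predicts week-12 ROM; the protocol gives no correlation from which to quantify that.

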## Methods/design

### Study design and setting

This is a prospective, multi-center, assessor-blinded randomized controlled study. Breast cancer patients who underwent breast cancer surgery in two university hospitals in South Korea (Samsung Medical Center, Sungkyunkwan University School of Medicine and Seoul St. Mary’s Hospital, College of Medicine, The Catholic University of Korea) will be recruited. The enrolled participants will be randomly allocated to either the digital healthcare rehabilitation group or the brochure-based rehabilitation group. Both groups will receive rehabilitation for 8 weeks. A flowchart of the study design is shown in Fig. 2.

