### Randomization, allocation concealment, and blinding

Participants meeting the eligibility criteria will be randomly assigned to either the digital healthcare or brochure-based rehabilitation group, in a 1:1 ratio using a block randomization procedure through computer-generated sequences with block size of four. One research team member will independently allocate the participants to groups using the sequences generated by computer. The researchers involved in the randomization process will not participate in the enrollment and assessment processes, and the allocation will be concealed by sealed notes. Therefore, both the participants and researchers involved in enrollment and assessment will be blinded to the allocation process. An experienced physical or occupational therapist blinded to the group allocations will assess the primary outcome.

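### The stated primary test cannot use hospital in a two-hospital trial; it remains valid, but a hospital term would be a cheap gain in precision

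*Protocol article*

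**What the plan says.** Under Study design and setting, the article states "This is a prospective, multi-center, assessor-blinded randomized controlled study" and describes the source of patients as "Breast cancer patients who underwent breast cancer surgery in two university hospitals in South Korea". The section on randomization allocates "in a 1:1 ratio using a block randomization procedure through computer-generated sequences with block size of four". It names no stratification factor and does not say whether each hospital has its own list.

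Under Outcome measures, "The primary outcome of the study is the change in ROM (flexion or abduction) in the affected shoulder between baseline and 12 weeks". Under Data analysis, "The primary outcome will be analyzed using the independent" *t* "test or Mann–Whitney test, depending on the normality of the data". For the other endpoints, "The secondary outcomes will be analyzed using a linear mixed model or generalized estimating equation", with no covariates listed. Nowhere in the article does hospital appear as a stratum, a covariate or the subject of a sensitivity analysis.

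**The concern.** Two hospitals can differ in case mix, in concurrent cancer treatment and so in how quickly shoulder ROM recovers. A plain two-sample test treats that difference as noise. Two situations are possible, and the article does not say which applies:

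- **Separate block list per hospital.** The arms are then nearly balanced on hospital. The plain test ignores this balance and uses a standard error that is too large.
- **One list for both hospitals.** Hospital mix can differ between arms by chance, and the plain test cannot adjust for it.

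What is at stake is precision in a trial planned with little spare power. Hospital is known for every patient, so using it requires no new data.

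**Working it through.** **Inputs from the article (Sample size section).** SD 23°, difference 15°, alpha 5% (taken as two-sided; the article does not say), power 80%, dropout 20%, 50 enrolled per arm. **Assumptions.** Hospital difference in ROM change *D* from 0° to 20°; hospitals of equal size (*q* = 0.5), with 70:30 as a check; 23° applies to ROM change; dropout is random.

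**1. The plan's own figures.** n = 2 × (1.960 + 0.842)² × 23² / 15² = 36.9, so 37 per arm. 37 / 0.8 = 46.25, so 47. Both agree with the article. Enrolling 50 leaves 50 × 0.8 = 40 completers per arm. The standard error is then 23 × √(2/40) = 5.14°, 15 / 5.14 = 2.917, and power is Φ(2.917 − 1.960) = 83.1% (82.1% from the *t* distribution).

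**2. Effect of omitting hospital.** Overall variance = within-hospital variance + q(1 − q)D². The article does not say which variance 23° represents, so both readings are shown, at 40 per arm by the normal formula.

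| D | 23° is within-hospital: overall SD | power, stated test | power with term | n per arm, stated test | 23° is overall: within SD | power, stated test | power with term |
|---|---|---|---|---|---|---|---|
| 0° | 23.00 | 83.1% | 83.1% | 37 | 23.00 | 83.1% | 83.1% |
| 5° | 23.14 | 82.6% | 83.1% | 38 | 22.86 | 83.1% | 83.5% |
| 10° | 23.54 | 81.3% | 83.1% | 39 | 22.45 | 83.1% | 84.8% |
| 15° | 24.19 | 79.2% | 83.1% | 41 | 21.74 | 83.1% | 87.0% |
| 20° | 25.08 | 76.3% | 83.1% | 44 | 20.71 | 83.1% | 90.0% |

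For example, at 10°: √(529 + 25) = 23.54 and √(529 − 25) = 22.45. With a 70:30 split and 23° as the within-hospital SD, the stated test has 81.6% at 10° and 77.3% at 20°, so the loss is slightly smaller.

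**3. Chance imbalance with one list.** With two equal hospitals and *m* patients per arm, the arm difference in hospital share has SD (2/m) × √[m × 0.25 × m/(2m − 1)]. This is 0.101 for m = 50 and 0.113 for m = 40. At 40 completers per arm, the resulting shift in the estimate has SD 1.13° for D = 10° and 2.25° for D = 20° (95% of trials within about 2.2° and 4.4°).

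This is the same quantity as the precision loss in step 2, not an addition to it. At D = 20°, √(5.14² + 2.25²) = 5.61°, and the plain test's own standard error is 25.08 × √(2/40) = 5.61°.

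**4. Standard error with separate lists.** If the arms are balanced on hospital, the plain test's standard error is too large by 23.54/23, about 2%, at 10° and by 25.08/23, about 9%, at 20°.

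**5. Simulation check.** 8,000 trials per setting, 100 enrolled, 20% random dropout, blocks of four, within-hospital SD 23°, *t* test against a linear model with hospital.

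| Lists | D | power, *t* test | power, with hospital | type I error, *t* test | type I error, with hospital |
|---|---|---|---|---|---|
| one | 0° | 81.4% | 80.9% | 4.7% | 4.7% |
| one | 10° | 79.8% | 80.9% | 4.8% | 4.7% |
| one | 20° | 74.9% | 81.5% | 5.0% | 5.0% |
| per hospital | 0° | 81.9% | 81.9% | 5.2% | 5.1% |
| per hospital | 10° | 80.3% | 81.6% | 4.8% | 5.1% |
| per hospital | 20° | 76.7% | 82.0% | 3.8% | 5.4% |

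The *t* test's mean estimates lay between 14.96° and 15.02° for a true 15°. The Mann–Whitney branch was not calculated.

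**The case against.** The strongest defence is that nothing here is invalid. With one list, type I error stays near 5% and the estimate is right on average. With separate lists, the plain test errs on the conservative side. That stands, and it makes this a matter of efficiency.

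The size is also wholly assumed. Hospital differences of 15° and 20° in ROM change equal or exceed the planned treatment effect, and nothing in the article suggests them. At 10° the stated test would need 39 per arm and about 40 are expected, so the target power is met by the planning formula. If 23° is the overall SD, the stated test has about 83% power whatever the hospital difference. These points stand as well.

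The mechanism is narrower than it first looks. Both arms exercise at home from the same programme. Because the outcome is change from baseline, a constant difference in assessor or goniometer reading between hospitals cancels. Only a difference in recovery matters.

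A reader might infer that hospital imbalance biases the result, or that it adds a shift of several degrees on top of the power loss. The figures do not support either reading: the shift is sampling variation already contained in the test's standard error. A reader might also infer that randomization was not stratified by hospital. The article neither says nor rules this out, and a condensed report commonly leaves that detail to the full protocol.

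The defence that an unseen SAP may deal with hospital is only partial. The article names the primary test, and an SAP that added hospital would depart from it.

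**Conclusion.** The point holds as a modest improvement to a valid analysis. With 23° as the within-hospital SD, the loss from omitting hospital is nil at 0°, 1 to 2 points at 10°, and 6 to 7 points at 20° (about 5 in the simulation with lists per hospital). With 23° as the overall SD nothing is lost against the plan; a gain of about 2 points at 10° or 7 at 20° is forgone. The hospital term is not better in every case: with no hospital difference it costs up to about half a point.

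The conclusion rests on an assumed range for the hospital difference, 40 completers per arm, hospitals of about equal size, and 23° applying to ROM change. At a difference of 10° or less the practical consequence is small.

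**What to change.** In the Data analysis section (and in the SAP, if there is one), state before results by arm are seen that the primary comparison is a linear model of 12-week ROM change on arm and hospital, with hospital as a fixed two-level factor. If a rank test is kept, make it hospital-stratified. Put the same hospital term in the models for the secondary outcomes. It would help to record, in the same place, whether block lists are kept per hospital.

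The cost is one degree of freedom, and under 1 power point if the hospitals do not differ. No extra patients, visits or data are needed.

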## Discussion

Limitations of shoulder ROM after breast cancer surgery are common, and physical therapy is known to be effective [2–6, 12]. Patients usually receive physical therapy by attending the rehabilitation center. However, it is difficult for those living in remote areas to attend the center. In that case, brochure-based physical therapy could be considered, though feedback on exercise is not possible. With the advance of the technology, there have been efforts to apply VR and AR system in exercise [21–23]. AR-based system enables those in remote areas to receive real-time feedback on exercise. Nonetheless, studies on post-operative breast cancer patients are scarce. Although one study examined breast cancer patients post-operatively using an Xbox Kinect-based VR system, the program involved game-based motion rather than physician-prescribed exercises [13].

To our knowledge, this will be the first randomized controlled study to use an AR system for post-operative rehabilitation of breast cancer patients. Using UINCARE Home+, physicians can customize exercise programs for individual patients and receive real-time feedback on exercise accuracy and adherence. This new type of customized physical therapy program incorporating feedback may be valuable to breast cancer patients with postoperative shoulder dysfunction, especially those living in remote areas. Moreover, due to the worldwide COVID-19 pandemic, it has become difficult to provide rehabilitation therapy to patients at the hospital. In such situations, AR-based treatment is expected to be useful. In the future, AR-based physical therapy may be considered as effective tool to manage shoulder dysfunction after breast cancer surgery in addition to traditional physical therapy.

In conclusion, this study will compare the clinical efficacy of a newly developed, AR-based real-time interactive digital healthcare system with that of a brochure-based rehabilitation program, in terms of the post-operative shoulder ROM of breast cancer patients.

## Trial status

The protocol presented here was finalized in March 2020 and is version 1.0, and there is no plan to change the current protocol. The first participant recruitment began on 16 April 2020, and the study is expected to be completed at June 2022.

## Data Availability

This manuscript does not contain any dataset, and no datasets were generated or analyzed during the study. The corresponding authors will have access to the final dataset of the trial.

